## Abstract

**Background:**

Gastric cancer is a common malignant tumor, and radical gastrectomy can markedly improve the prognosis of gastric cancer patients. However, some patients are diagnosed with advanced gastric cancer before receiving any antitumor therapy and need to receive neoadjuvant chemotherapy (NACT). Previous studies have shown that NACT may cause gut barrier dysfunction and intestinal dysbacteriosis which may further lead to infections. Probiotics have the potential to reduce postoperative infections and improve short-term outcomes after abdominal surgery; however, no large-sample, multicenter, randomized clinical trials have been conducted to explore the effectiveness of probiotics in gastric cancer patients receiving NACT. So we proposed a hypothesis that probiotics can improve short-term outcomes after minimally invasive radical gastrectomy in gastric cancer patients receiving NACT and designed this multicenter randomized controlled trial with the objective to verify this hypothesis.

**Methods/design:**

The GISSG 2023–01 study will be a prospective, open-label, multicenter RCT to verify whether perioperatively probiotic supplementation (begin from the end of the last cycle of NACT to postoperative day 7 or the discharge day) can reduce postoperative infections and improve recovery of gastrointestinal function and other short-term outcomes after minimally invasive radical gastrectomy in gastric cancer patients receiving NACT. A total of 318 patients who meet the inclusion criteria will be enrolled in this study and randomly divided into two groups in a 1:1 ratio: the probiotic group (*n* = 159) and the control group (*n* = 159). The participants in the probiotic group will receive perioperative probiotic supplementation, and those in the control group will receive blank control management. The other perioperative management protocols will be the same between the two groups. The primary outcome is postoperative infection compared between the two groups, and the secondary outcomes are postoperative recovery of gastrointestinal function, quality of life, laboratory parameters of systemic inflammation and other short-term outcomes.

**Discussion:**

The results of this RCT should clarify whether perioperative probiotic supplementation would reduce postoperative infection, promote recovery of gastrointestinal function, reduce laboratory parameters of systemic inflammation and improve symptoms and quality of life after minimally invasive radical gastrectomy in gastric cancer patients receiving NACT. It is hoped that our data will provide evidence that probiotic supplementation improves short-term outcomes in gastric cancer patients receiving NACT.

**Trial registration:**

This trial has been registered on https://clinicaltrials.gov/(NCT05901779).

**Supplementary Information:**

The online version contains supplementary material available at 10.1186/s12885-025-14115-x.

## Introduction

### Background and rationale

Gastric cancer is a common malignant tumor accounting for 5.6% of new cases and causes 7.7% new deaths of all global cases of cancer [1]. Some patients are diagnosed with advanced gastric cancer (AGC) before receiving any anticancer therapy, which poses challenges to the treatment and prognosis of these individuals. Although D2 radical gastrectomy is a standard and preferred surgical protocol for AGC [2], the high tumor burden, micrometastasis and high recurrence risk still impair the therapeutic effect of surgery.

At present, the treatment of locally AGC is centered on surgery and guided by multidisciplinary team advice [3]. Since the first report of applying NACT in treating gastric cancer [4], many studies have focused on the advantages of NACT. The MAGIC study showed that NACT can markedly shrink tumor size and prolong the overall survival, five-year survival rate and progression-free survival of patients with resectable adenocarcinoma of the stomach, esophagogastric junction, or lower esophagus [5]. The RESOLVE study provided evidence that compared with adjuvant CapOX (capecitabine combined with oxaliplatin), perioperative SOX (S- 1 combined with oxaliplatin) can improve the 3-year disease-free survival of patients with locally advanced gastric or gastroesophageal junction adenocarcinoma undergoing D2 gastrectomy [6]. Schuhmacher et al. demonstrated that NACT can shrink the tumor size, decrease the number of lymph node metastases, improve pN0 rate and improve the chance of R0 resection [7]. Although there are many advantages of NACT in treating AGC, it may increase postoperative complications such as incision infection and anastomotic leakage [7]. Our previous study showed that NACT may increase postoperative infections, leading to damage to gut barrier function (low expression of tight junction-related proteins and tight junction disruption) and gut dysbiosis (depletion of beneficial commensal bacteria and loss of microbiota diversity) [8]. 5-FU is widely used in NACT for gastric cancer. Previous studies showed 5-FU when given to rats has multiple effects on the gut and causes mucosal damage and disrupts the gut microbiota [9–11].

Probiotics are defined as “live microorganisms which when administered in adequate amounts confer a health benefit on the host” [12]. The specific mechanism of probiotic action is unclear, and current assumptions include direct antimicrobial activity and indirect competitive inhibition. Due to the side effects of NACT on the gut barrier and microbiota, many studies have focused on the functions of probiotics to explore their capacity to reverse those side effects. Yuan et al. found that *Bifidobacterium infantis* can maintain the normal mucosal structure, increase the expression of PCNA (proliferating cell nuclear antigen), and reduce the expression of NF-κB, proinflammatory factors and MPO (myeloperoxidase). These data suggest that the probiotic *B. infantis* is effective in reducing chemotherapy-induced intestinal mucositis in rats [9]. Justino et al. drew a similar conclusion as Yuan, although the probiotic they used was *Lactobacillus acidophilus* [10]*.* In surgical patients, intraoperative stress may cause an increase in intestinal permeability, gut dysbiosis and bacterial translocation, which are important pathogenic factors that increase postoperative infections. For this reason, the introduction of probiotics is expected to maintain the intestinal barrier function by decreasing abnormal intestinal permeability, reducing both intestinal inflammation and the release of cytokines and maintaining the dynamic balance of normal gut microbiota. The short-term effects of probiotics, for example the reduction of postoperative infections have been explored in pancreatobiliary surgery, liver transplant surgery, and colon and rectal surgery [13–20]. Although our previous single-center RCT appeared to suggest that perioperative probiotic supplements can reduce postoperative infections and improve recovery of gastrointestinal function in gastric cancer patients receiving neoadjuvant chemotherapy [21], these results need to be verified by a rigorously designed, large-sample RCT. There have been a large number of clinical trials exploring the effects of probiotics or synbiotics on the clinical outcomes of patients undergoing abdominal surgeries, but no multicenter, large sample RCT has focused on the effects of probiotics on the postoperative short-term clinical outcomes of gastric cancer patients receiving NACT.

### Objective

The aim of this study was to investigate the effects of probiotics on infectious complications, recovery of gastrointestinal function, laboratory parameters of systemic inflammation, quality of life and other short-term outcomes after laparoscopic or DaVinci robotic minimally invasive radical gastrectomy in gastric cancer patients who have completed NACT.

### Trial design

The GISSG 2023–01 study is designed as a multicenter open-label parallel-randomized superiority controlled clinical trial. All eligible participants will be randomized into a probiotic group and a blank control group in a 1:1 ratio. The intervention duration will begin from the end of the last cycle of NACT to postoperative day (POD) 7 or the discharge day.

## Methods

The SPIRIT 2013 guidelines were followed for the construction of this report (Fig. 1) [22]. The CONSORT flowchart is shown in Fig. 2.

**Fig. 1 Fig1:**
[figure not shown]
The enrollment, intervention and assessment items in the flowchart. The symbol × represents that the program needs to be collected. − 1, the end of the last cycle of preoperative chemotherapy; 0, from the end of the last cycle of preoperative chemotherapy to admission for surgery; D1, postoperative day 1; D2, postoperative day 2; D3, postoperative day 3; D4, postoperative day 4; D5, postoperative day 5; D6, postoperative day 6; D7, postoperative day 7; D30, postoperative day 30; Dp, prolonged postoperative hospital stay; * the majority of participants can be discharged before D7 under the ERAS perioperative management protocol, but if any situation prolongs the hospital stay, the marked items should be recorded and described on the CRF

**Fig. 2 Fig2:**
[figure not shown]
The CONSORT flowchart

#### Eligibility criteria

Patients with AGC who have completed NACT will be screened for eligibility.

The inclusion criteria are as follows: 18–80 years old; both male and female; clinical stage of T3/4 N + evaluated by CT/MR/EUS at new diagnosis (before any anticancer treatment), completion of 2–4 cycles preoperative chemotherapy based on 5-FU (such as SOX, XELOX, FLOT, etc.) at 3–6 weeks before surgery; ASA grade of I-III; radical minimally invasive gastrectomy via a laparoscope or a DaVinci surgical system judged as possible; histologically confirmed gastric adenocarcinoma; ECOG score of 0 ~ 1; and provision of written informed consent before entering the study screening process.

The exclusion criteria are as follows: need for emergency surgery due to perforation and/or obstruction; receipt of antibiotics and/or glucocorticoids within 14 days before surgery; presence of bacterial infection and/or autoimmune disease and/or IBD; intolerance or allergy to probiotics; major upper abdominal surgery history (for example laparoscopic cholecystectomy); use of probiotics within 7 days before the intervention; current participation in other clinical trials; severe mental illness; inability to participate in this trial due to severe disease of other organs evaluated by researchers, such as severe cardiac insufficiency (LVEF < 30%, NYHA > II, severe arrhythmia, congestive heart failure, myocardial infarction within 6 months), liver dysfunction (Child‒Pugh C), renal dysfunction (need for hemodialysis); need for simultaneous surgery; lactation or pregnancy; refusal to participate in this trial.

Patients from the 22 hospitals will be evaluated, and those who meet the eligibility criteria will be invited to participate in the study. Patients will decide whether they are willing to participate in this study, and for those participants, written informed consent will be required.

The surgeons who perform the minimally invasive radical gastrectomy for the participants will also be evaluated. They should have performed more than 100 DaVinci robotic or laparoscopic radical gastrectomies and send an unedited operation radio to the sponsor investigators to verify their capacity.

### Interventions, surgery and perioperative management

Patients in the probiotic group will receive three probiotic capsules (BIFICO, live combined *Bifidobacterium*, *Lactobacillus* and *Enterococcus* capsules, Shanghai Sine Pharmaceutical Co. Ltd., [name], Shanghai, China) containing *Bifidobacterium longum, Lactobacillus acidophilus,* and *Enterococcus faecalis* twice per day. Each capsule will contain > 1 * 10^7^ colony-forming units (CFUs) of live bacteria. Patients in the control group will be managed with a blank control. The intervention duration will begin from the end of the last cycle of NACT to postoperative day (POD) 7 or the discharge day. Adherence to the intervention protocols will be checked by telephone before admission to the surgical departments and making the rounds of the wards after admission. If any adverse event associated with the intervention occurs, the intervention will be stopped after evaluation by the investigators.

All enrolled patients will adhere to a perioperative enhanced recovery after surgery (ERAS) protocol [23]. The ERAS program involves preoperative prehabilitation [24] (including physical and respiratory training, nutritional support and psychosocial treatment), no preoperative mechanical bowel preparation, fasting 6 h before surgery and oral glucose solution ingestion allowed until 2 h before surgery, intraoperative target-oriented liquid management, local anesthesia in the deep incision, general anesthesia combined with epidural anesthesia, early removal of the urinary catheter and abdominal drainage tube, early bedside activity, multimodal postoperative analgesia, and postoperative early food ingestion under the guidance of surgeons (from liquid to semi-liquid then solid food according to the tolerance of patients).

Laparoscopic or DaVinci robotic radical gastrectomy will be performed by surgeons from the 22 hospitals whose capacity evaluation is described above. Surgical procedures will be guided by *Japanese Gastric Cancer Treatment Guidelines 2021 (6 th edition)* [2]. The type of digestive tract reconstruction will depend on the habits, intraoperative status and past experience of the surgeons, and the choice of laparoscopy- or DaVinci-assisted surgery will depend on the patients’ choice.

Notably, all participants cannot intake any drugs containing probiotics and/or prebiotics during the study. Prophylactic antibiotic use is allowed during the operation and should be stopped within 24 h after surgery. Therapeutic antibiotics are allowed to be prescribed if postoperative infections occur, and the type and duration of antibiotic use are based on clinical experience and bacteriologic evidence.

### Outcomes

The primary outcome is the incidence of postoperative infectious complications, which are defined as bacterial infections occurring within 30 d after surgery. The definition of infectious complications is based on fever (≥ 38 °C), elevation of C-reactive protein (CRP), specific clinical symptoms of infection and positive bacterial culture. The diagnostic criteria for postoperative infections in this study are as follows. Pneumonia [25]: fever, cough, dyspnea, reduced arterial oxygen, typical pulmonary infiltrate on chest X-ray, positive culture from sputum or bronchoalveolar lavage. Urinary tract infection: obvious symptoms including frequent micturition, urgency to urinate, urodynia, leukocyturia, and a positive urine culture with > 10^5^ CFU/ml. Incision infection: redness or swelling of the incision, subcutaneous gas accumulation and purulent secretion and positive culture of incisional secretion [26]. Intraabdominal infection [27]: abdominal symptoms and positive signs such as abdominal pain, tenderness, rebound tenderness, radiographic evidence including intra-abdominal abscess, positive bacterial cultures from intra-abdominal smears or abdominal drainage fluid. Catheter-related blood stream infection: refer to the guidelines [28]. Systemic inflammatory response syndrome (SIRS): two or more of the following: a, temperature > 38 °C or < 36 °C; b, heart rate > 90/min; c, respiratory rate > 20/min or PaCO2 < 32 mm Hg (4.3 kPa); d, white blood cell count > 12 000/mm^3^ or < 4000/mm^3^ or > 10% immature bands [29]. The diagnosis of sepsis should follow the *Sepsis- 3 Consensus* [30].

Secondary outcomes for all participants include blood test results, such as the leukocyte count (WBC), percent of neutrophils (NEUT%), CRP and procalcitonin on PODs 1, 3, and 5; postoperative body temperature; length of postoperative hospital stay (LOS); total cost of hospitalization; 30-d readmission rate; 30-d mortality rate; duration of therapeutic antibiotic use; time to first flatus, first bowel movement and solid food tolerance; time to initiating adjuvant chemotherapy; EORTC QLQ-C30 score [31] on POD 30; PGSAS- 45 score [32] on PODs 3, 5 and 30; and visual analogue scale for pain evaluation on PODs 1, 3 and 5.

### Sample size

The sample size calculation was based on postoperative infection. Based on the results of our previous single-center RCT, the rates of postoperative infectious complications were 39.4% in the control group and 15.2% in the probiotic group. Given a significance one-sided level of *α* = 0.025 and test efficiency of 1 − *β* = 80%, a loss adjustment of 10% and a superiority threshold of 10%, the total sample requires at least 318 patients (159 in the test group and 159 in the control group on a 1:1 allocation ratio). The Test for Two Proportions (Non-Zero Null Hypothesis[Differences]) was used for sample size calculation (Hintze, J. (2011). PASS 11. NCSS, LLC. Kaysville, Utah, USA. www.ncss.com/).

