### Statistical methods

The Shapiro‒Wilk test will be used to verify the normality of the quantitative variables. To describe the quantitative variables, the mean and SD will be used, and the median and interquartile range will be used for those variables that do not follow a normal distribution. For qualitative variable descriptions, frequencies and percentages will be used. A contrast test of proportions will be based on the *χ*^*2*^ test or Fisher’s exact test. Quantitative variables will be analyzed by Student’s *t* test or two-way repeated-measures analysis. The Mann‒Whitney *U* test will be used for variables that do not follow a normal distribution. The results will be analyzed using SPSS version 24 (IBM, Armonk, NY, USA), and *P* < 0.05 will be considered statistically significant. The mean of each variable will be used to replace missing data.

A modified intention-to-treat analysis (mITT) and per-protocol (PP) analysis will be used to compare outcomes, but the conclusion will be drawn from mITT analysis.

The mITT population is defined as subjects who are screened by investigators according to the inclusion and exclusion criteria, randomized into certain groups and receive at least one intervention. The PP population is defined as those who complete the given intervention, adhere to the study protocol and complete the data collection. Subgroup analysis will be executed based on the operation platform (laparoscope or DaVinci surgical robot), preoperative chemotherapy regimens (SOX, DOS, XELOX, FLOT or others), GI restruction and resection range (proximal, distal or total gastrectomy).

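### The sample size is built on showing a reduction of more than 10 points, but the analysis named for proportions tests only a difference of zero

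*Protocol article*

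**What the plan says.** The Sample size section takes its event rates from the group's previous single-center trial: "the rates of postoperative infectious complications were 39.4% in the control group and 15.2% in the probiotic group". It sets the error level with "Given a significance one-sided level of *α* = 0.025", asks for 80% power, and adds "a loss adjustment of 10% and a superiority threshold of 10%, the total sample requires at least 318 patients", which it splits as "159 in the test group and 159 in the control group on a 1:1 allocation ratio". It also names the procedure: "The Test for Two Proportions (Non-Zero Null Hypothesis[Differences]) was used for sample size calculation".

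The Statistical methods section sets the analysis. It says "A contrast test of proportions will be based on the" chi-square test or Fisher's exact test, and that a P value below "0.05 will be considered statistically significant". It gives no margin, no shifted null hypothesis and no confidence limit to be compared with 10 points. It draws the conclusion from the modified intention-to-treat population.

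The Trial design section calls the trial a superiority trial without mentioning a margin. The threshold appears only in the Sample size section.

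**The concern.** Two different null hypotheses are in use. The trial was sized to reject a reduction of 10 points or less. The tests named for the analysis reject a reduction of zero. Only one of them can be the success criterion for the primary outcome, and the article does not say which.

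A result that shows some reduction, but does not exclude one below 10 points, could be reported as success under the Statistical methods section or as failure under the Sample size section. The power statement is also affected, because 80% describes a test that the analysis section does not contain.

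The gap matters in practice. The planning difference of 24.2 points comes from one single-center trial, and the Background section says its results still need verification. A smaller effect across 22 centers could easily fall where the two rules disagree.

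**Working it through.** **Inputs**, all from the Sample size section: control rate 0.394; probiotic rate 0.152; difference 0.394 − 0.152 = 0.242; threshold 0.10; one-sided alpha 0.025 (z = 1.960); power 80% (z = 0.842); loss 10%; 1:1 allocation.

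**1. Reproducing 318.** The formula for a non-zero null with unpooled variance is

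n per arm = (1.960 + 0.842)² × (0.394 × 0.606 + 0.152 × 0.848) / (0.242 − 0.10)² = 143.1.

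Allowing for 10% loss, 143.1 / 0.9 = 159.0 per arm, or 318 in total. The stated figure is reproduced, so the threshold is a real part of the design and is absolute (10 percentage points).

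**2. The same inputs with a zero null.** The usual two-proportion formula gives 52.0, so 53 per arm. After 10% loss this is 59 per arm, or 118 in total (134 with a continuity correction). About 318 − 118 = 200 of the planned patients are there because of the 10-point null.

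**3. Power at the planning rates, 143 per arm.**
- Test against 10 points: standard error = √(0.36766 / 143) = 0.0507; 0.142 / 0.0507 − 1.960 = 0.84; power 80.0%.
- Chi-square: null standard error = √(2 × 0.273 × 0.727 / 143) = 0.0527; (0.242 − 1.960 × 0.0527) / 0.0507 = 2.74; power 99.7%.

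**4. Observed reduction needed, with 39.4% observed in the control arm.**

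| Evaluable per arm | Chi-square significant from | Reduction above 10 points shown from |
|---|---|---|
| 143 | 11.0 points | 20.3 points |
| 159 | 10.5 points | 19.8 points |

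Check at 143 per arm:
- Chi-square: 0.110 / √(2 × 0.339 × 0.661 / 143) = 1.96.
- Threshold test: (0.203 − 0.10) / √((0.394 × 0.606 + 0.191 × 0.809) / 143) = 1.96.

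**5. True reduction of exactly 10 points (39.4% against 29.4%).** Chi-square is significant in 43% of trials with 143 per arm and in 47% with 159. The test against 10 points rejects at its nominal 2.5%.

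**6. How often the rules disagree (143 per arm).** Passing the threshold test implies passing chi-square, so the chance of disagreement is the difference between the two rejection rates. At the planning rates it is 99.7% − 80.0%, about 20%. At a true reduction of 10 points it is 43% − 2.5%, about 40%.

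**The case against.** The strongest reply is that the article never states a hypothesis of more than 10 points. Its Abstract, Objective and Trial design sections speak of improving outcomes, reducing infections and superiority, and a zero-null test answers those aims. On this reading the analysis is right and only the sample-size rationale is out of line. The trial is then overpowered, and type I error for the claim that probiotics reduce infection is not inflated. One-sided 0.025 and two-sided 0.05 also agree in the direction of benefit. All of this is correct. It means that the 43% figure is an error rate only for the claim that the threshold was passed. It does not remove the contradiction: the threshold was chosen, it drives about 200 of the 318 patients, and the reader is not told what role it plays in the conclusion.

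A second reply is that the sentence on proportions is generic and that an unseen analysis plan may add a test against the threshold. That is possible. However, the primary outcome is a proportion, and the section names both its test and its significance criterion. The point rests on two statements that conflict, not on missing detail.

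A third reply concerns the remedy. A score method does not keep exactly 80% power with 318 patients: Farrington-Manning gives 78.7% with 143 per arm, and would need 148 per arm (330 in total after loss) for 80%. This stands, and the shortfall is small.

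**Conclusion.** The concern holds. The Sample size section and the Statistical methods section use different null hypotheses for the primary outcome, and the 10-point threshold is not carried into the analysis. The figure of 318 is not arithmetically wrong, and chi-square remains a valid test of zero difference. The faults are that the success criterion is left ambiguous and that the stated power does not belong to the named test.

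The size of the problem is a band of observed reductions from about 11 to 20 points in which the two rules give opposite answers. These limits assume a 39.4% control rate and 143 evaluable patients per arm. They move to about 10.5 and 19.8 points with 159 per arm, and would shift with a different control rate. Because this concerns the success criterion of the primary outcome, it must be settled before the results are interpreted.

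**What to change.** State the primary analysis as the risk difference (control minus probiotic) in the modified intention-to-treat population, with a two-sided 95% confidence interval by a score method (Farrington-Manning or Miettinen-Nurminen). Fix the reading in advance:

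- Lower limit above 10 points: superiority by the stated threshold is shown.
- Lower limit above 0 but not above 10 points: infection is reduced, but the threshold is not shown.
- Lower limit at or below 0: no reduction is shown.

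The hypotheses are nested and all three readings come from one interval, so no extra alpha is needed.

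If the sponsor did not intend the threshold as a success criterion, the alternative is to say so, state a zero-null hypothesis, and give the power of that test (99.7% at the planning rates with 143 per arm). The account of how 318 was obtained should then stay on record.

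The Trial status section reports that recruitment is complete and that the trial ended during peer review. Either change should therefore be a dated and disclosed clarification, and the report should say whether it was made before the outcome data were compared.

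The cost is wording only, with no further patients. The drawbacks are a stricter bar for any claim about the threshold, and power of 78.7% instead of 80% for that claim under a Farrington-Manning analysis with 143 per arm.
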